## Abstract

**Background:**

Wheelchair users live predominantly sedentary lifestyles and have a substantially higher risk for cardiometabolic disease and mortality compared to people without disabilities. Exercise training has been found to be effective in improving cardiometabolic health (CMH) outcomes among people without disabilities, but research on wheelchair users is limited and of poor quality.

**Objective:**

The primary aim of this study is to examine the immediate and sustained effects of a 24-week, telehealth, movement-to-music cardiovascular (M2M-C) exercise program on core indicators of CMH among adult wheelchair users compared to an active control group. The secondary aim is to explore the beneficial effects of M2M-C exercises on cardiovascular capacity, physical activity, and quality of life. Intervention components include tailored exercises and remote performance monitoring, delivered via live videoconference training by a telecoach and asynchronous videos.

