To test whether the M2M program can improve CMH outcomes among wheelchair users, this study uses a parallel-group RCT with blinded assessors. The intervention group will use the M2M program, composed primarily of cardiovascular exercises (M2M-C), which will be compared to an active control condition using prerecorded non-M2M exercise videos. The M2M-C exercises were informed by disability exercise guidelines and reviews of relevant studies [22]. This study is referred to as the Cardiometabolic Health Intervention Using Music and Exercise (CHIME) study. The primary aim is to examine the effects of a 24-week, synchronous M2M-C program on core indicators of CMH in adult wheelchair users with ≥2 cardiometabolic risk factors. The secondary aim will explore the beneficial effects of M2M-C exercises on cardiovascular capacity, physical activity, and quality of life. We hypothesize the M2M-C intervention will yield both immediate and sustained CMH outcomes among adult wheelchair users with poor cardiometabolic profiles.

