### Outcomes

Outcomes are assessed at baseline, midintervention (12 wk), postintervention (24 wk), and follow-up (36 wk) time points. Physiological outcomes are assessed by anonymous-to-treatment assessors. The assessors are not involved in random assignment or the intervention delivery and do not directly communicate with the M2M instructors and assistant health coaches about participants. Data collection with physiological outcomes is conducted at a local research facility affiliated with a major medical center. Self-reported outcomes are administrated via a secure electronic database, referred to as REDCap. Online platform analytics are used to assess heart rate (HR) and video minutes viewed and stored in the cloud. Figure 1 shows the schedule of assessments.

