Once the baseline assessment is completed, participants are randomly assigned to either the intervention or control conditions using a random numbers sequence with concealed allocation. The project coordinator unfolds the allocation information via this study’s database, communicates the condition of assignment with the participant and, if allocated to the M2M-C intervention, prepares the necessary equipment for program participation. The participant will also meet with instructors and assistant telecoaches. If allocated to the control condition (SET), the project coordinator prepares the tablet with access to the SET videos. Lastly, the project coordinator will schedule a goal-setting session to be completed within 2 weeks between the participant and PI. This is carried out for both groups.

Participants in both intervention and control groups receive a 15-minute, individual goal-setting session at each time point from the PI, who is trained in physical activity counseling. They discuss participant’s outcome expectations from the program and review the goal of the program based on the given exercise prescription. The participants are prompted to share any foreseen barriers to complying with the program and guided to develop a relapse prevention plan (eg, identifying activities and social support to reactivate participation; outlining consequences for continuing and discontinuing the program). Additionally, the participants are prompted to share additional health goals and receive guidance on making them specific, measurable, attainable, relevant, and time-bound.

The intervention and control participants complete the same measurement procedures at the 12-week (midintervention) and the 24-week (postintervention) time points. There is no physiological data collection at the 36-week follow-up, as the aim to be addressed is sustaining physical activity behavior.

Participants receive up to US $830 for completing the measures per assessment period, including baseline as well as 12-, 24-, and 36-week assessments, and 12- and 24-week interviews. Semistructured exit interviews are conducted at the 24-week assessment for the first 30 participants to identify opportunities for intervention improvement and refinement.

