## Discussion

### Principal Findings

The CHIME study proposes a parallel-group RCT for examining the 24-week effects of an evidence-based M2M program compared with a control condition for yielding immediate and sustained CMH outcomes among adult wheelchair users with poor cardiometabolic profiles. This study anticipates that after 24 weeks, participants in the M2M-C intervention group will show significant improvements in key cardiometabolic risk factors, such as reduced HbA_1c_ levels; lower fasting glucose and triglycerides; and decreased BP, waist circumference, and body fat percentage, compared to the control group. Furthermore, the M2M-C intervention is expected to improve health-related physical fitness, including measurements such as VO_2peak_, FEV1, FVC, and grip strength, in line with self-reported psychosocial health outcomes. In addition to the improvements in CMH and physical fitness, we anticipate that these benefits will be sustained during the maintenance phase (up to 36 wk). This suggests that wheelchair users may be able to adhere to telehealth-based exercise programs over the long term. If successful, this study will be the largest and sufficiently powered confirmatory RCT trial targeting CMH outcomes in this population. The prescribed exercise dose was informed by the review of the relevant literature [22]. If successful, this study will establish an evidence-based recommendation of adequate exercise dosing for adult wheelchair users with poor CMH profiles.

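### Sustained cardiometabolic benefit is claimed in the abstract, Introduction and Discussion, but no physiological outcome is measured after training ends at week 24

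*Protocol article*

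**What the plan says.** Three places claim a lasting effect on CMH.

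- Abstract, Objective: the primary aim is to "examine the immediate and sustained effects of a 24-week, telehealth, movement-to-music cardiovascular (M2M-C) exercise program on core indicators of CMH", compared with an active control. No week is given.
- Introduction, Rationale for Telehealth Exercise Program: "We hypothesize the M2M-C intervention will yield both immediate and sustained CMH outcomes". Again no week is given. The primary aim stated just before it does not use the word *sustained*.
- Discussion, Principal Findings: the program is to be examined "compared with a control condition for yielding immediate and sustained CMH outcomes among adult wheelchair users with poor cardiometabolic profiles", and after listing improvements in CMH and fitness the authors write "we anticipate that these benefits will be sustained during the maintenance phase (up to 36 wk". This is the only place that ties CMH benefit to week 36.

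The Methods say otherwise.

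- Aims and Design of this Study limits the primary aim to the immediate effect of 24 weeks of training, with a hypothesis running from baseline to week 24. The sustained effect, weeks 24 to 36, is a tertiary aim on physical activity participation only.
- Procedure repeats the baseline measurements at weeks 12 and 24 and then states: "There is no physiological data collection at the 36-week follow-up, as the aim to be addressed is sustaining physical activity behavior".
- Outcomes gives one schedule for everything: "Outcomes are assessed at baseline, midintervention (12 wk), postintervention (24 wk), and follow-up (36 wk) time points".
- Data Analyses, Tertiary Aims, attaches the sustained label to the week-24 visit and restricts that analysis to within-group changes.

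**The concern.** Showing that a benefit persists after coaching stops requires measuring it after coaching stops. The document promises or expects this for CMH in three places and rules out the necessary measurements in a fourth.

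The label in Tertiary Aims adds to the difficulty. If the analysis follows that text, a change seen at the end of training, within one arm, would carry the name sustained effect. A reader who also has the abstract's objective in mind could take it as evidence of durability. Principal Findings presents the trial as confirmatory and as a basis for a recommendation on exercise dosing, so the stated claim should match what the data can show.

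**Working it through.** The point concerns which outcomes are measured when, so the check is mainly a comparison of sections.

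**Step 1. Are the primary outcomes physiological?** Primary Outcome Measures lists nine entries: hsCRP; HbA1c; fasting insulin; fasting glucose with HOMA-IR; triglycerides; cholesterol; blood pressure; waist circumference; and BMI with DXA body composition. All come from blood, a cuff or a body measurement. The fitness measures named in Principal Findings (VO2peak, FEV1, FVC, grip strength) are laboratory tests as well.

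**Step 2. When are they measured?** Under Procedure, at baseline, week 12 and week 24, and not at week 36. Training ends at week 24. The count of CMH entries with a post-training value is therefore 0 of 9, and of the four fitness measures 0 of 4.

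**Step 3. What can be estimated?** Persistence is the change from week 24 to week 36, or the between-group difference at week 36. Both need a week-36 value. With none, neither can be estimated in either arm, whatever the sample size.

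**Step 4. What does *sustained* mean in each section?**

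| Section | Outcome | Immediate | Sustained |
|---|---|---|---|
| Abstract, Objective | CMH | no week given | no week given |
| Introduction, hypothesis | CMH | no week given | no week given |
| Methods, Aims and Design | CMH (primary); physical activity (tertiary) | baseline to week 24 (CMH) | weeks 24 to 36 (physical activity only) |
| Data Analyses, Primary and Secondary Aims | primary and secondary outcomes | week 12 | not used |
| Data Analyses, Tertiary Aims | tertiary aims | not used | week 24, within group |
| Discussion, Principal Findings | CMH and fitness | after 24 weeks | up to week 36 |

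The Methods aims and the Procedure section agree with each other. The abstract, Introduction and Discussion do not fit them, and neither does the label in Tertiary Aims. As described there, the sustained analysis stops at week 24 and so does not reach the period that the tertiary aim defines.

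**Step 5. Is the sample size affected?** The plan's figure reproduces. With 50 per group and d = 0.566, the noncentrality is 0.566 × √(50/2) = 2.83 on 98 degrees of freedom. A two-sided 5% t test then has 80.0% power. For total cholesterol, 24.4/43 = 0.567 gives 80.2%; for triglycerides, 12.7/22.4 = 0.567 gives 80.1%; for body fat, 2.5/4.3 = 0.581 gives 82.1%. Average attrition is (33 + 13)/2 = 23%, and 132 × 0.77 = 101.6 completers, against the 100 required. Nothing in this calculation depends on week 36, so narrowing the claim leaves it unchanged.

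**The case against.** The strongest defence is that the section that fixes the aims is already right. Aims and Design limits the primary aim to week 24 and gives the sustained question to physical activity, and Procedure gives that as the reason for taking no physiology at week 36. On this view the fault is loose wording in summary and narrative text. This stands as a limit on the point. A reader might infer that the trial cannot answer its primary objective, or that half of it has no data. That holds only for the abstract's wording, and only if *sustained* there means after training. The Methods version can be answered in full.

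A second defence is that *sustained* may mean week 24, as in Tertiary Aims, where CMH data do exist. This does not rescue the text. Aims and Design defines sustained as weeks 24 to 36 and treats the 24-week effect as immediate. The Tertiary Aims analysis is within-group only, while the abstract promises a comparison with control. Nor can it help Principal Findings, which names week 36.

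Four further inferences go beyond the document.

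- That all three claims extend to week 36. Only Principal Findings names that week.
- That a week-24 result will be published as durability. No section says so. The label creates the risk, and the Discussion statement is an expectation, not a reporting rule.
- That maintenance is covered by self-report alone. Outcomes also describes platform analytics (heart rate and video minutes), and nothing says these stop at week 24. They are not CMH outcomes, so the point is unaffected.
- That the schedule fails to show which outcomes are taken at week 36. Outcomes refers to Figure 1 for this, and the figure is not available here. Only the sentence in the text can be called too broad.

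**Conclusion.** The point holds as an inconsistency between sections. The sustained CMH claim in the abstract and Introduction, and the week-36 expectation for CMH and fitness in the Discussion, have no post-training physiological data behind them: 0 of 9 primary outcome entries and 0 of 4 fitness measures. The label on week 24 in Tertiary Aims conflicts with the definition in Aims and Design. The primary aim as the Methods state it is sound and answerable, and power and sample size are unaffected.

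The conclusion rests on the explicit statement in Procedure that no physiology is collected at week 36, and on reading *sustained* as Aims and Design defines it. It does not depend on Figure 1. The use of *immediate* for week 12 under Primary and Secondary Aims is a related but separate timing conflict, and this point does not rely on it.

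**What to change.** 1. In the abstract's Objective, the Introduction's hypothesis and Principal Findings, limit the CMH and fitness claims to week 24, and reserve *sustained* for physical activity from week 24 to week 36, as Aims and Design already does.
2. In Tertiary Aims, remove the sustained label from the week-24 visit and tie the sustained analysis to the week 24-to-36 physical activity data.
3. Under Outcomes, state that physiological outcomes are not taken at week 36, as Procedure says.

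These are wording changes. They need no new visit and leave the 132 participants and the power calculation as they are. The price is a narrower claim: the trial will not speak to the durability of CMH or fitness gains. If the investigators want to keep that claim, they would have to measure these outcomes at week 36. The document gives no week-36 effect or SD from which power for that comparison could be calculated.

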**Methods:**

This study’s design is a parallel-arm randomized controlled trial enrolling 132 physically inactive adult wheelchair users with poor cardiometabolic profiles. The M2M-C intervention group involves 24 weeks of virtual live and monitored home exercise training (3×/wk, 15-40 min/session), followed by a 12-week maintenance period where participants have access to an online media library of exercise videos. The control group involves 36 weeks of self-guided exercise through access to a media library of exercise videos, including videos for range of motion, muscle strength, and balance. The primary outcomes are cardiometabolic indicators of health, and assessors are blinded.

**Results:**

Recruitment procedures started in January 2024 with the first participant enrolled on March 18, 2024. All data are anticipated to be collected by November 2027, and the main results of the trial are anticipated to be published by February 2028. Secondary analyses of data will be subsequently published. A total of 16 participants have been recruited as of paper submission.

**Conclusions:**

The knowledge obtained from this trial will provide evidence to inform exercise prescriptions aimed at improving CMH among adult wheelchair users.

**Trial Registration:**

ClinicalTrials.gov NCT05606432; https://clinicaltrials.gov/study/NCT05606432

**International Registered Report Identifier (IRRID):**

DERR1-10.2196/57423

## Introduction

### Background

People with physical disabilities have higher risks of cardiometabolic disease than the general population. For example, studies have reported that as many as one-third of people with spinal cord injury (SCI) may be diagnosed with cardiometabolic disease (ranging from n=41, 29% to n=222, 34.1%), which is nearly twice as prevalent as reported in people without SCI [1-3]. Another study found that adults living with cerebral palsy or spina bifida are 52% more likely to experience any type of cardiometabolic morbidity than adults without cerebral palsy or spina bifida (n=15,302) [4]. Meta-analyses have demonstrated that conventional aerobic exercise, such as running, walking, and cycling at a moderate-to-vigorous intensity, are effective in managing indicators of cardiometabolic health (CMH) in the general population [5-9]. However, people with physical disabilities, particularly wheelchair users, are typically unable to engage in conventional modalities of exercise long enough to obtain CMH benefits. Wheelchair users include users of any wheeled devices for their primary means of mobility, such as manual and powered wheelchairs or motorized scooters, and may include individuals in a variety of disability groups, including those with SCI, cerebral palsy, spina bifida, multiple sclerosis, or limb loss. A total of roughly 5.5 million wheelchair users in the United States would benefit from an accessible aerobic exercise program to reduce their cardiometabolic disease risk [10].

However, there is limited evidence that aerobic exercise improves CMH among wheelchair users. Most evidence is observational and nearly all randomized controlled trials (RCTs) have small sample sizes limited to a single population (eg, those with SCI). There are no large confirmatory RCTs that demonstrate that aerobic exercise improves CMH in adult wheelchair users. A recent meta-analysis of 3 RCTs, with samples of 15-21 adults with SCI, determined that 6-weeks of aerobic exercise improved CMH among adults with SCI (ie, decreased fasting glucose and insulin and increased fasting high-density lipoprotein cholesterol fraction) [11]. Another meta-analysis of 16 pre-post and controlled trials with sample sizes of 5-20 adults with SCI determined that vigorous exercise training improved cardiorespiratory fitness in adults with SCI [12] (ie, increased peak power output, muscular strength, and time to fatigue) but did not improve CMH risk factors, such as blood pressure (BP), cholesterol, and insulin sensitivity. Noted limitations of these studies included small sample sizes, inclusion of participants already within healthy ranges for CMH at baseline, lack of a control group, use of laboratory-based training, and inclusion of a single population (those with SCI). Therefore, the finding that CMH measures did not improve must be interpreted with caution.

Interventions that have sought to improve physical activity levels have also failed to improve CMH among wheelchair users. The largest physical activity trial among wheelchair users (n=128), Workout on Wheels, increased self-reported physical activity by 17 min/wk, with no significant between-group differences in cardiorespiratory fitness or CMH measures [13]. Other recent lifestyle interventions (eg, behavioral coaching) have similarly failed to elicit significant CMH benefits among people with disabilities, even while achieving large sample sizes [14]. Thus, the exercise doses or intensity studied may be suboptimal for improving CMH among people with physical disabilities. Despite failures to improve CMH, many of these physical activity trials have informed the creation of the most recent guideline related to CMH for people with SCI [15,16]. Collectively, there is an urgent need for well-designed interventions that can provide an effective exercise dose for people with disabilities, including wheelchair users, while obtaining evidence for improving CMH through physical activity.

### Rationale for Telehealth Exercise Program

A telehealth exercise program was developed to overcome the barriers of participation in exercise requiring individuals to leave their homes and use expensive equipment. This study uses an exercise program that includes various movement patterns that are coupled with elements of music and imagery, referred to as movement to music (M2M) [17]. The M2M program uses a range of different muscle groups allowing for a safer form of exercise than arm ergometry. Moreover, M2M incorporates a theory-driven telehealth delivery protocol that removes the most common barriers to participation in community and clinical exercise training studies (ie, cost, transportation, and time) [18,19]. The design of the movement-to-music cardiovascular (M2M-C) intervention is based on four key elements of social cognitive theory: self-efficacy, self-regulation, outcome expectations, and social support. These components are essential for promoting positive health behavior change. To effectively integrate these principles, the M2M-C program provides a structured, individualized, and progressively challenging exercise routine. Participants receive regular feedback and personalized guidance from M2M-C instructors and telecoaches, which helps build confidence and maintain motivation. In addition, the incorporation of music enhances movement quality and motor coordination [20] while serving as a powerful motivational tool [21]. By increasing enjoyment and improving mood, music makes exercise more appealing and engaging. This approach is consistent with the broader goal of promoting sustained physical activity among wheelchair users by addressing both psychological and physical barriers to exercise adherence.

To test whether the M2M program can improve CMH outcomes among wheelchair users, this study uses a parallel-group RCT with blinded assessors. The intervention group will use the M2M program, composed primarily of cardiovascular exercises (M2M-C), which will be compared to an active control condition using prerecorded non-M2M exercise videos. The M2M-C exercises were informed by disability exercise guidelines and reviews of relevant studies [22]. This study is referred to as the Cardiometabolic Health Intervention Using Music and Exercise (CHIME) study. The primary aim is to examine the effects of a 24-week, synchronous M2M-C program on core indicators of CMH in adult wheelchair users with ≥2 cardiometabolic risk factors. The secondary aim will explore the beneficial effects of M2M-C exercises on cardiovascular capacity, physical activity, and quality of life. We hypothesize the M2M-C intervention will yield both immediate and sustained CMH outcomes among adult wheelchair users with poor cardiometabolic profiles.

## Methods

### Study Design

This study’s protocol follows the SPIRIT (Standard Protocol Items: Recommendations for Interventional Trials) guidelines [23,24].

### Aims and Design of this Study

This study’s design includes three aims. The primary aim examines the immediate effect of a 24-week, synchronous M2M-C training protocol compared to a 24-week, asynchronous activity control on core indicators of CMH among 132 adult wheelchair users with ≥2 cardiometabolic risk factors. The secondary aim examines the immediate effect of M2M-C training compared to the active control condition on cardiovascular capacity, physical activity, and quality of life. The first tertiary aim evaluates the sustained effects of M2M-C training (24 to 36 wk) on physical activity participation. A second tertiary aim evaluates the potential response heterogeneity in CMH, cardiovascular capacity, and physical activity outcomes using prespecified moderator variables (eg, age, sex, body composition, diet, or ethnicity) to understand for whom the intervention is most effective.

This study’s aims will be tested using a parallel-group, assessor-blinded RCT design. For primary and secondary aims, we hypothesize that a telehealth M2M-C program will lead to significantly greater improvements in CMH outcomes, peak oxygen consumption (VO_2peak_), physical activity level, and quality of life from baseline to 24 weeks compared to controls. For the tertiary aim 1, we hypothesize that M2M-C participants will maintain physical activity levels from week 24 to week 36.

